# Effect of different weekly frequencies of Chen-style Tai Chi in elders with chronic non-specific low back pain: study protocol for a randomised controlled trial

**DOI:** 10.1186/s13063-022-06909-2

**Published:** 2022-11-22

**Keywords:** Tai Chi, Chronic Low back pain, Old people, Different frequency, Randomised controlled trial

## Abstract

**Background:**

Tai Chi (TC), as one of mild to moderate exercise therapies specifically recommended by clinical practice guideline from the American College of Physician, is a viable option for chronic non-specific low back pain (CNLBP) treatment. Nevertheless, limited studies focused on the effect of different weekly frequencies of TC in elders with CNLBP. This superiority study aims to compare the differences of TC with different weekly frequencies in elders with CNLBP on the premise of proving its effectiveness, and identifying whether mindfulness mediates the effect of TC on treatment outcomes.

**Methods:**

In total, 284 senior citizens with CNLBP will be recruited in this single-centre, randomised, single-blinded (outcome assessors, data managers and the statistician), parallel controlled trial. Participants will be randomly divided into either one of three TC groups (1, 3, or 5 sessions/week, on the basis of weekly health educational lectures) or weekly health educational lectures, sustaining for 12 weeks, followed by 12 weeks of follow-up after the end of intervention. The primary outcome (the changes of LBP intensity at rest) will be measured at baseline before randomisation and immediately after the completion of weeks 4, 8 and 12 of the intervention, and the end of follow-up (week 24) using the visual analogue scale (VAS, 0–10 cm) to put a mark on the VAS scale to show how severities of their average low back pain have been over the past 24 h. Secondary outcomes, including Beck Depression Inventory-II, Pain Catastrophising Scale and Five Facet Mindfulness Questionnaire, Oswestry Disability Index and Short Form-36, will be measured at baseline and immediately after the completion of week 12 of the intervention and end of follow-up. The intention-to-treat and per-protocol principles will be used to analyse outcomes with a setting at *α* = 0.05 as statistical significance.

**Discussion:**

This comprehensive and detailed protocol will be the first trial to compare the effectiveness of different weekly frequencies of TC in elders with CNLBP. The outcomes may provide valuable data about the choice of the ideal number of sessions to further normalise the application of exercise for clinicians.

**Trial registration:**

Chinese clinical trial registry ChiCTR2200058190. Registered on 1 April 2022.

**Supplementary Information:**

The online version contains supplementary material available at 10.1186/s13063-022-06909-2.

## Introduction

Pain occurring below the costal margin and above the buttock folds can be defined as low back pain (LBP). The majority of patients with LBP have a group of clinical subtypes collectively known as non-specific low back pain (NLBP), in which most of the events have no definite causes [1] and chronic NLBP (CNLBP) is NLBP that lasts 12 weeks or longer [2, 3]. The lifetime prevalence rate of LBP is 84%, amongst which CNLBP accounts for almost one third of cases, especially in elders [4], affecting nearly 20–25% of the population older than 65 years. Although LBP is not a fatal disease, it is the foremost leading cause of physical disability worldwide [5], ranking sixth in the overall cause of disease burden (disability-adjusted life years) [2]. Pain induces serious psychological or medical pathology, which incurs a huge burden on society in terms of medical health and lost productivity. Furthermore, identifying effective non-pharmacological approaches for old people with CNLBP is urgently needed because of the risks of surgery and drug abuse. However, specific novel alternative treatments for pain are still unclear. Hence, although the effect size of traditional interventions is moderate [6, 7], these are still worthy of further exploration.

Tai Chi (TC) is one of mind-body exercise therapies specifically recommended by clinical practice guideline from the American College of Physician [6] and is broadly applied to different age groups worldwide [8]. The latest American Physical Therapy Association guidelines on LBP management in elderly also recommended a variety of general exercise training for conservative treatment. An exercise training should restore or improve the overall strength or endurance of major muscle groups in the upper/lower extremities and trunk; such exercises include exercises for flexibility/mobility and aerobic/conditioning exercises [9], which indicates TC may be a CNLBP-modifying treatment option. Meanwhile, pain relief has been found to play an important role in the movement and quality of life (QOL) of patients suffering from LBP [10]. TC combines slow, gentle movements with deep breathing and mental focus, can fully activate abdominal core muscles, improve pulmonary ventilation in patients with LBP [11], strengthen the stability of lumbar bone structure [12] and promote the improvement of lumbar proprioception [13, 14]. To a certain extent, it may alleviate pain, pleasure, improve participants’ self-efficacy and mitigate CNLBP patients with anxiety and/or depression mood.

A majority of previous studies chose TC intervention in patients with chronic pain for 60 min at a time for 12 weeks is relatively common [15–18]. Patients with LBP who have comorbidities are eager to relieve symptoms as quickly as possible. For elders without TC foundation, completing a set of integrated TC learning in a short time is unrealistic [16, 19]. Hence, selecting a part of core muscle with high activation levels for specific familiarisation and training in the preliminary exercise can shorten the learning time of TC and may be more in line with the psychological expectations of patients for symptom improvement efficiency. Chen-style TC with 16 forms may be an optimal choice for the elderly. It has the following characteristics. Firstly, it can be readily understood by elders. Secondly, the difficulty of movement gradually increases, and weight bearing gradually changes from bilateral support to unilateral support. Thirdly, the speed of movements constantly changes, which may increase the interest in TC training. However, whether different weekly frequencies of TC training (i.e. fewer or more sessions in the same week) may relieve pain in the elderly is still unknown, and pain trajectories have not been identified.

Some studies showed TC to be effective for treatment of CNLBP, reporting positive outcomes such as reduction in pain or psychological distress such as depression and anxiety, reduction in pain-related disability and improved functional ability [16, 17, 20, 21], but few studies have focused specifically on older adults especially older people with CNLBP. Given the promising data from younger adults [20, 21], the value of TC for older adults with CNLBP remains worthy of investigation. Only two studies have looked at the role of TC in the elderly with CNLBP [22, 23], but both have some limitations. Lee et al.’s study [22] demonstrated the multifaceted benefits of TC for the elderly with CNLBP, but this study is only a qualitative study and the sample size is seriously insufficient (*n*=18). Sherman et al.’s study [23] confirmed that TC intervention is feasible and acceptable in the elderly with CNLBP, but in terms of sample size, it has the same methodological problems as the above studies. Besides, its primary outcome did not focus on the effect of TC on pain relief in elderly patients with CNLBP. A meta-analysis showed that there were significant heterogeneity and quality differences in the results of TC intervention with LBP, which may be caused by differences in dose (such as frequency, duration, course of treatment and mode) [18], which is also potentially suggestive that the dose of TC is an important factor affecting its effectiveness. Recent meta-analyses related to TC have also revealed that researchers should concentrate more on the timing and frequency of TC training, in order to make clearer claims about its beneficial effects [24, 25]. The lack of information has led to the severe under-utilisation of conventional exercise by clinicians and the poor exercise compliance of patients.

In light of the abovementioned studies, the primary objective of this study will compare the differences in the curative effects of TC with different weekly frequencies in elders over 60 years [26, 27] with CNLBP on the premise of proving its effectiveness. Besides, we will also identify whether mindfulness mediates the intervention effect of TC. We hypothesised that high weekly frequencies (five times a week) of TC intervention may be more beneficial to pain, physical and psychosocial functioning and QOL in elderly with CNLBP than low (once a week) and moderate weekly frequencies (three times a week) TC intervention, and that the higher the baseline mindfulness level of participants, the better the effect of TC on CNLBP symptoms. The interventions are relatively safe. The results of this trial are expected to help clinicians and future researchers provide references in selecting the ideal TC dose and standardise the formulation of TC exercise prescription for patients with CNLBP, and enrich the theoretical basis for TC dose selection. For patients, we expect the results of this study to provide evidence-based advice for treatment planning for patients with CNLBP and to use TC as an ideal form of self-care to relieve their symptoms and improve QOL.

## Methods and analysis

### Trial design

This study is a single-centre, randomised, single-blinded (outcome assessors, data managers and the statistician), parallel controlled trial, which will be carried out in Changsha First Social Welfare Institute, Hunan Province, China. In total, 284 eligible participants with CNLBP will be randomly and equally divided into four groups in a 1:1:1:1 allocation ratio. Three experimental groups will undergo 12 weeks of supervised TC training and complete one, three or five TC sessions weekly, respectively. The control group will not receive any rehabilitation programme. Meanwhile, all participants will receive weekly health lectures until the end of the 12-week intervention and will be required to maintain a healthy lifestyle, afterwards followed by 12 weeks of follow-up after the end of the intervention.

The primary outcome (the changes of LBP intensity at rest) will be measured at baseline before randomisation and immediately after the completion of week 4, week 8, week 12 of the intervention and the end of follow-up (week 24). The secondary outcomes will be measured at baseline before randomisation and immediately after the completion of week 12 of the intervention and the end of follow-up (week 24). The details of the time schedule of this trial are shown in Table 1. The recommendations of the Consolidated Standards of Reporting Trials (CONSORT) will be strictly followed, and the protocol will be reported in line with the Standard Protocol Items (SPIRIT) [28] (Additional file 2). The flow chart is presented in Fig. 1.

**Table 1 Tab1:**
[figure not shown]
The schedule of enrollment, interventions and assessments according to SPIRIT items

**Fig. 1 Fig1:**
[figure not shown]
Flowchart of this trial. Notes: PP: Per-protocol; ITT: Intention-to-treat

### Patient and public involvement

The involvement of the public and patients is becoming a necessary part of health research [29]. Patients are often more aware of their disease and lifestyle needs than many medical professionals. They also have important ideas about which studies will be most beneficial to their lives, especially about how symptoms can be managed in a way that improves the QOL. We are inviting patients who have experienced or are experiencing CNLBP and those who are interested in the study, to join our community of interest (through social media, and by putting up recruitment posters outside Changsha First Social Welfare Institute, Hunan Province, China). The public and patient representatives (PPR) will be involved during the planning, conduction and analysis of the trial. The PPR group will meet every 2 months to provide peer support and share personal experiences.

### Participants

#### Recruitment and ethics

The enrollment programme will run from the fourth quarter of 2022, and follow-up work is expected to be completed in October 2023. A total of 284 participants will be recruited via the hospital bulletin and official website of Changsha First Social Welfare Institute and a wide range of media channels, including local advertisements and WeChat (a free popular communication application in China).

Any interviewee who volunteers to participate in the study will be requested to fill a screening assessment to identify their eligibility. The participants will be informed of the study details, such as interventions, potential benefits, specific training schedule (including date and time) and some announcements to avoid potential risks and control confounding factors. In addition, all participants will sign informed consent before the study begins.

This study was approved by the Ethics Committee of Changsha Social Work College (CSMZ2022002) and registered at the Chinese Clinical Trial Registry (ChiCTR2200058190). It will be carried out in accordance with the Declaration of Helsinki.

#### Eligibility criteria

This trial will include the following: participants who are right-handed; adults aged 60 years or above [26, 27]; diagnosed with CNLBP for at least 3 months in line with the CNLBP definition of the National Institutes of Health (NIH) [30]; VAS score ≥ 4 [31]; Mini-Mental Status Examination (MMSE) score ≥ 24 [32]; no habitual regular exercise and TC training history in the past 6 months; able to ambulate independently and participate in TC training.

The exclusion criteria include the following: LBP caused by mandatory spondylitis, malignant tumours, vertebral fractures and spinal infection; serious diseases that limit ability to participate in TC training, including dementia, neurological disease, symptomatic heart or vascular disease (angina, peripheral vascular disease, congestive heart failure and severe hypertension), recent stroke, severe insulin-dependent diabetes mellitus, psychiatric disease, renal disease, liver disease, active cancer or anaemia; having analgesic drugs or regular physical therapy programmes for CNLBP within the past year; participating in a similar study within the past year and could have significant impact on the results of this study; planning to move permanently from the area during the trial period.

The withdrawal criteria comprise occurrence of severe adverse events (e.g. nausea, vomiting, palpitations) during the study and patients deemed unsuitable to continue the trial by specialist doctors; and voluntary withdrawal from the trial for any reason at any time.

#### Sample size

The sample size was estimated using the PASS software (ver. 15.0). Limited studies have focused on the effect of different weekly frequencies of TC in elders with CNLBP. As such, the primary indicator was the changes of LBP intensity at rest (represented as VAS, score of 0–10). The sample size was calculated via the minimum clinically important difference of 2 on the VAS of pain intensity, and expecting the standard deviation of 2.2 immediately following TC training [33–35]. Considering the multiple comparison, the Bonferroni adjustment was applied, a sample with 240 participants was needed with a power of 80% and an alpha of 0.05 (*α*=0.05 is the overall allowable type I error in the comparisons between each experimental group and the control group sequentially). Moreover, considering a 15% attrition rate, at least 71 participants per group will be needed in this protocol trial [Total participants: 240/ (1−0.15) ≈ 284 participants, considering an equal allocation of 1:1:1:1 to four groups].

### Randomisation and blinding

The simple stochastic method will be applied in this study. SPSS 24.0 (IBM, Inc., Chicago, USA) software will be used by a statistician who is not involved in this study to generate a random number sequence. Random numbers with the group allocation code will be kept in opaque and sealed envelopes, which will be prepared by a person who is not involved in the whole process of the study, including recruitment, enrollment, evaluation and statistical analysis of data and random assignment the participants to the four groups (word “1” or “2” or “3” or “4”) with equal probability according to the order of entry. Random assignment results in all enrolled eligible participants will be informed by telephone after completing baseline assessment data collection and signing an informed consent form.

Considering the nature of TC, blinding the participants and TC coaches during the process of TC training is completely impossible. Hence, outcome assessors, data managers and the statistician will be blinded in this trial, and the blind will be kept by the custodian of the random sequence, who is not participating in the process of participant recruitment, intervention, outcome evaluation and data statistical analysis. Upon completion of all data analysis, the random sequence custodian will reveal the treatment allocations.

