### Study intervention

#### Experimental group: TC training

The trial protocol will be administered at the Sports Centre of Changsha First Social Institute. A total of 284 eligible participants will be randomly divided into four groups. Amongst these, three groups (group 1, group 2 and group 3) will undergo TC training with different frequencies (one, three or five sessions/week, 60 min/session, sustain for 12 weeks). Before the training begins, each group will be assigned a coach. The participants will be familiarised with the TC programme, including principles, practice strategies and safety considerations, through printed materials and short videos a week prior to study initiation. Three research assistants will supervise and guide the participants’ learning conditions through weekly phone calls.

At the beginning of this study, participants of three TC groups will commence the interventions at the same time under the guidance and supervision of coaches to prevent seasonal changes in disease severity. Group 1 will practice Chen-style TC one time a week for 12 weeks under the guidance of a coach with 10 years of teaching experience. The TC training programme shall be jointly formulated by the research group members and coaches after discussion. See Figs. 2 and 3 for the movements included in TC. The whole training process includes 10 min of warm-up, 40 min of TC training and 10 min of cooling down. The details are shown in Additional file 1. Sessions for the first week are designed to enable participants to master each training movement, breathing technique and relaxation method under the guidance of the instructors. The remaining sessions will consist of the following sections: (1) warming-up and review of TC principles and techniques; (2) Chen-style TC with 16 forms for two times; (3) breathing mechanics and (4) cooling down. Meanwhile, video recordings will be used to monitor the quality of TC training and offer feedback to coaches on time throughout the study. For group 2 and group 3, the parameters will be in line with group 1, except that training frequency will be transferred to 3 times a week and 5 times a week, respectively.

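### Simple randomisation is named, but the plan states four equal arms of at least 71 out of 284, a split that this method almost never gives

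*Protocol article*

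**What the plan says.** Three sections of the protocol article bear on arm size.

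- **Randomisation and blinding** names the method: "The simple stochastic method will be applied in this study". A statistician outside the study generates a random number sequence in SPSS, the codes go into sealed opaque envelopes, and participants are assigned to groups 1 to 4 "with equal probability according to the order of entry". No blocks, strata or fixed arm totals are mentioned.
- **Trial design** says that the 284 participants "will be randomly and equally divided into four groups in a 1:1:1:1 allocation ratio".
- **Sample size** starts from 240 evaluable participants, allows for 15% attrition, and concludes that "at least 71 participants per group will be needed in this protocol trial", assuming equal allocation to the four groups.

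**The concern.** Under simple randomisation each assignment is an independent draw, so arm sizes are left to chance and are equal only in expectation. The other two sections describe an equal split and a minimum per arm. The minimum uses up the whole sample, so any arm above 71 forces another below it.

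What is at stake is whether the trial will have the arm sizes on which its sample size rests. Every planned test compares two arms: each Tai Chi group with control, then the Tai Chi groups with one another. The precision of each test depends on the two realised arm sizes.

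**Working it through.** **Inputs, all from the protocol article**
- Total randomised: 284. Four groups with probability 1/4 each, assigned in order of entry.
- Stated minimum: 71 per group. Evaluable target: 240, or 240/4 = 60 per group. Attrition: 15%.
- Difference 2, SD 2.2, power 80% (Sample size); alpha 0.0167 per comparison with control (Statistical analysis). Sidedness is not stated; two-sided is assumed here.

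**Step 1. The plan's own figures.**
The attrition step reproduces: 60 / 0.85 = 70.6, rounded up to 71, and 4 × 71 = 284.

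The 240 does not follow from the stated inputs. With z-values 2.394 (two-sided 0.05/3) and 0.842 (80% power), n per arm = 2 × (2.394 + 0.842)² × 2.2² / 2² = 25.3, so 26 per arm, or 104 in total. That is a separate matter. The present point needs only the stated 71 and 284.

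**Step 2. Chance of meeting the stated minimum.**
Because 4 × 71 = 284, all arms reach 71 only if each has exactly 71:

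P = 284! / (71!⁴ × 4²⁸⁴) = 0.00021, about 1 in 4,700.

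**Step 3. What simple randomisation gives instead.**
The SD of one arm is √(284 × 0.25 × 0.75) = 7.3, and the 95% range for one arm is 57 to 86. One million simulated multinomial allocations give:

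| Quantity | Result |
|---|---|
| Smallest arm, mean | 62.4 |
| Smallest arm, median (95% range) | 63 (53 to 69) |
| Largest arm, mean | about 80 |
| Largest minus smallest, median (95% range) | 17 (5 to 34) |
| P(some arm below 60 before attrition) | 22% |

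An arm of 62 leaves about 62 × 0.85 = 53 after the planned attrition, against the 60 intended.

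**Step 4. Effect on precision.**
For two arms of size a and b, the SE relative to 71 v 71 is √(1/a + 1/b) / √(2/71). Over simulated allocations this ratio averages 1.005, and its 95th percentile is about 1.06. Two examples:
- 62 v 80: 1.008
- 62 v 71: 1.036

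**Step 5. Effect on power, under two assumptions.**
- *At the stated difference of 2, SD 2.2 and alpha 0.0167* (t-based): 71 v 71 gives 99.8%, and 48 v 60 completers still gives 98.7%.
- *If 60 per arm truly gives only 80%*, as the protocol claims: the SE for 53 v 60 is √[(1/53 + 1/60) / (2/60)] = 1.032 times that for 60 v 60. Power is then Φ(3.236/1.032 − 2.394) = Φ(0.74), about 77%. For 48 v 60 it is about 74%.

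**Step 6. What would meet the stated minimum.**
Blocks of 4 give 284/4 = 71 complete blocks and exactly 71 per arm. If simple randomisation were kept and the minimum enforced, about 344 participants would be needed for a 90% chance that every arm reaches 71, and about 352 to 356 for 95%.

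**The case against.** The strongest reply is that an allocation ratio is a target, which equal probabilities meet in expectation, and that dividing a planned total by four is ordinary sample-size practice and promises no realised count. That is fair for the ratio itself. It does not cover the statements that participants are divided equally and that each group needs at least 71. Those describe realised counts, and the named method does not secure them.

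A second reply is that the sealed envelopes may be a fixed set of 71 per group, shuffled. That would give equal arms while each participant still had a 1/4 chance of each group. The article does not describe such a set and calls the method simple. If a fixed set was meant, the method is misnamed, and one sentence corrects it.

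A third reply is that simple randomisation is valid and is the least predictable method, which has value where participants and coaches are unblinded. This stands, and it is why a restricted list needs care with concealment.

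A reader might also infer larger harms, which the documents do not support:
- **Bias or an invalid analysis.** Chance imbalance in arm size does not bias the comparisons, and the planned ANCOVA does not need equal arms.
- **A small control arm weakening all three first-step tests.** Control has an expected size of 71 and is as likely to be the largest arm as the smallest. The figure of 62 is the expected minimum over four arms, not the expected control arm.
- **Drift over calendar time.** Under Study intervention, the three Tai Chi groups start together, expressly to guard against seasonal change. That sentence does not name the control group, but nothing in the article shows that drift would matter.
- **A serious loss of power.** Step 5 of the working does not bear this out on either assumption.

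**Conclusion.** The inconsistency is real and lies in what the article states, not in detail that it leaves out. Read literally, equal arms of at least 71 out of 284 occur with probability about 0.0002 under the named method. The expected smallest arm is about 62, and about one allocation in five (22%) leaves some arm below 60 before anyone drops out.

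The consequence is modest: an average pairwise SE inflation of about 0.5%, about 6% at the 95th percentile. Power stays near 99% at the stated inputs, or falls from 80% to about 77% for 53 v 60 completers if the protocol's own power claim is taken as true.

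These figures assume independent assignment with probability 1/4, exactly 284 randomised and two-sided tests. The correction is worth making because it is cheap and makes the stated arm size true. It is not needed to rescue the validity of the trial.

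**What to change.** Before enrolment, replace the list with a concealed, restricted 1:1:1:1 list and name the method under Randomisation and blinding. Either of two forms would do:

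1. Permuted blocks of randomly varying size (for example 4 and 8), with block sizes hidden from recruiters.
2. One random permutation of 284 codes, 71 per group.

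The sealed envelopes and the independent custodian stay as planned. If a fixed set of envelopes was always intended, say so in place of the present description.

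If simple randomisation is kept, reword Trial design and Sample size so that 71 per arm is expected, not guaranteed.

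The cost is one new list and a few sentences; the ANCOVA and the staffing do not change. Trial status describes recruitment as still to begin. The small downside is slightly more predictable allocation in an open-label trial, which varying blocks or a single permuted list keep limited.
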